**Methods/Design:**

This will be a single-centre, single-blinded, randomised controlled trial with a parallel design, for which 68 patients undergoing total knee replacement will be recruited and followed up at 3, 6 and 12 months; 34 will be control patients who will receive the standard orthopaedic surgery treatment (electrocoagulation), and the other 34 will receive the same treatment plus 5 ml EVICEL™ applied during surgery and used according to the manufacturer’s instructions. The primary objective is to test the null hypothesis that the effect of EVICEL™ for controlling haemostasis and reducing postoperative blood loss in patients undergoing total knee replacement is not superior to the use of electrocoagulation alone. The secondary objective is to show that EVICEL™ reduces the need for transfusion, increases range of motion, improves clinical outcome and wound healing, and reduces the need for analgesics. The tertiary objective is to show that EVICEL™ reduces the costs of total knee replacement treatment.

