## Methods/Design

### Study design

This study will be a single-centre, parallel-design, randomised controlled trial (RCT) in which 68 patients undergoing TKR will be recruited according to the inclusion/exclusion criteria for RCTs, and treated within a 12-month period at the Department of Orthopaedic Surgery. It is registered in the German registry under number DRKS00007564. Ethical approval has been obtained from the Institutional Review Board of the Hannover Medical School under process number ‘6170 M mono’. The study will be conducted in accordance with the Helsinki Declaration.

Thirty-four (34) control patients will receive the standard orthopaedic surgery treatment (electrocoagulation). Another 34 will receive the same treatment as control patients plus 5 ml EVICEL™ applied during surgery and used according to the manufacturer’s instructions.

The main trial period is the stay in hospital for the surgery and postoperative surveillance. Follow-up examinations of all patients will be conducted 3, 6 and 12 months after surgery. With a recruitment period of 12 months and a follow-up period of 12 months, the total length of the study period is calculated to be approximately 24 months.

The study will be terminated when the necessary 34 patients per group have completed the study. Additionally, the sponsor has the right to terminate the study at any time for reasonable medical or administrative reasons. Also, the principal investigator can decide to terminate the study at any time for reasonable medical or administrative reasons.

The results manuscript will follow the advice from the CONSORT guide and its extension to cluster trials.

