For the overall cost of the treatment, differences in duration of hospital stay, as well as differences in the total cost of treatment between the two groups will be compared, including the need for physiotherapy. The length of the inpatient stay depends not only on the patient’s condition but also on social and organisational factors, such as the capacity of the inpatient rehabilitation centre. Therefore, a theoretical discharge date will be defined and evaluated in addition to the actual date. The theoretical discharge date is defined as the first day on which the patient achieves the following three criteria: a dry wound without signs of infection, maximum knee flexion of at least 90° and the ability to climb stairs using crutches.

For the sake of safety, patients will be under permanent surveillance during the operation. Adverse events (AEs) and serious adverse events (SAEs) will be documented. Clinical signs of infections will be monitored daily, and blood parameters collected regularly.

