### Study population

A total of 68 men or nonpregnant women scheduled for primary unilateral TKR will be recruited and treated in the context of this RCT.

The inclusion criteria are as follows:Men or women aged from 55 to 70 years on the day of the operation.Patients with an indication for primary TKR on the basis of diagnosed osteoarthritis, arthritis or avascular necrosis.Patients with intact medial and lateral collateral ligaments (to be diagnosed in the preoperative examination) who are planned preoperatively to receive a Stryker Triathlon CR or Triathlon PS system prosthesis.Patients willing to participate in this RCT and who have signed the informed consent form approved by the ethics committee.

The exclusion criteria are as follows:Patients participating in any other clinical trial within 30 days before inclusion or concurrent with this study.Pregnant or nursing women.Patients tested positive for HIV, hepatitis B and C.Patients with documented or suspected hypersensitivity to any of the active substances or excipients of EVICEL™, or to bone cement or its components.Patients with acute or suspected coagulation disorders and patients with preoperative blood parameters INR >1.4 or PTT >40 s.Concomitant medication within 7 days before surgery with substances that affect haemostasis, except for low molecular weight heparins or alternatives in prophylactic dosage indicated for standard thrombosis prophylaxis.Anaemic patients showing preoperative Hb levels <11 g/dl.Patients with a deficit in extension >15° or with a maximal flexion <90°.Highly obese people (BMI >35). Patients suffering from neuromuscular or neurosensory diseases. Patients with known active tumour disease or tumour-related diseases. Patients suffering from any significant concurrent disease, illness or psychiatric disorder that would compromise their safety or compliance, or interfere with consent, study participation, follow-up or interpretation of the results. Patients receiving a prosthesis different from the Stryker Triathlon CR or Triathlon PS system owing to intraoperative circumstances (for example, bone fractures or ligament insufficiencies). Intraoperative deviation from the agreed haemostatic procedure (for example, use of the tourniquet deviating from the agreement, for example in case of surgery lasting >2 h). Patients with surgery lasting >2 h will not be randomised.

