### Study procedure

On the day of admission eligible patients will be informed about the study protocol. If they agree to participate in the study and sign and date the informed consent form, the following procedure will apply (Table 1):

**Table 1 Tab1:** Schedule of events

Procedures	Baseline (within 72 h prior to procedure)	Day of surgery	Postoperative stay in hospital	3 Months after surgery ± 2 weeks	6 Months after surgery ± 2 weeks	12 Months after surgery ± 2 weeks
Inclusion/exclusion	X	X				
Randomisation		X				
Informed consent	X					
Demographics	X					
Medical history	X					
Concomitant medications including use of analgesics or peripheral nerve block	X	X	X^d^	X	X	X
Physical examination (ROM)	X		X^d^	X	X	X
Laboratory tests (virology^a^, CBC^b^, clinical chemistry^c^)	X^a–c^		X^e,b,c^			
Coagulation parameters (INR, PTT)	X					
Treatment application		X				
Intraoperative data assessment		X				
Clinical outcome score assessment (KSS/KOOS)	X		X^f^	X	X	X
Surgical site assessment			X^d^	X	X	X
Wound healing assessment			X^d^			
Assessment of patient’s mobility on crutches (stairs)			X^d^			
Adverse events		X	X^d^	X	X	X
Assessment of physiotherapy treatments after rehabilitation				X	X	X
Calculation of overall costs of TKR						X

^a^Virology: Hep B/C and HIV screening

^b^CBC: Hb, leucocytes

^c^Clinical chemistry: CRP

^d^Assessment daily during the visits (except for Sundays as for the physical examination)

^e^Assessment on days 2, 4 and 6 (+/− 1 day) and on day 7

^f^Assessment on day 7

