#### Statistical methods

The statistical analysis will be carried out at the end of the study; interim analyses are not intended. However, the analysis of the primary endpoint may be carried out earlier, as soon as the data from the last patient have been assessed. For this analysis, ANCOVA for Hb level differences baseline with respect to the detected minimum in the first 7 postoperative days for both treatment groups with adjustment for baseline Hb levels will be used. If the upper limit of the two-sided 95 % confidence interval (CI) of the difference in means between EVICEL™ and standard orthopaedic surgery as estimated from the ANCOVA model is <0, the superiority of EVICEL™ will be concluded. Missing values for Hb observations will be replaced by the last observation carried forward method (LOCF). If there are no postoperative Hb values available for a particular patient, that patient will be recorded as having the largest decrease in Hb of the control group.

AEs and SAEs will be evaluated descriptively by chi-squared tests.

For the secondary endpoints, the need for at least one transfusion will be analysed by odds ratios (OR) together with 95 % CIs. The ROM and the length of hospital stay will be analysed by *t*-tests. The total cost per patient will be analysed using Wilcoxon’s signed ranks test. Time until wound healing will be tested by log rank tests.

Secondary and tertiary analyses are exploratory and will be performed descriptively.

The *P* values will be assessed descriptively and will be deemed significant when *P* <0.05.

The primary analysis will be conducted on the intention to treat (ITT) population, that is, for all randomised patients. Sensitivity analyses will be performed in the per-protocol (PP) population, including all patients who completed the study according to the protocol.

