#### Randomisation/blinding

The process of randomisation is performed centrally by the Institute for Biometry. A randomisation list is created and assigns the patients to either the control group or the study group. When the surgical procedure arrives at the point at which EVICEL™ treatment has to be performed in the active group (after conventional haemostasis), the investigator then initiates the randomisation and queries the patient’s assignment at the Institute for Biometry by phone. This procedure allows the statement to be made that the operation prior to the application of EVICEL™ is concealed and performed without any bias.

In this RCT, the patients will be blinded but owing to the nature of the intervention the surgeons clearly cannot be blinded.

The treating surgeons will conduct the therapy in a way that complies with the single-blinded design of the study. In the rare case of a spinal anaesthesia, it will be ensured that patients will have no opportunity to realise whether they receive the medicinal product under investigation (IMP) or not. The medical team involved in the operation and patient’s care is responsible for keeping the treatment blinded. The nurses, physiotherapists and physicians collecting data after surgery will also be blinded to the treatment allocation.

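### Total cost is assigned a paired test (Wilcoxon signed ranks), although the trial compares two independent groups with one cost per patient: a minor but real correction to an exploratory analysis

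*Protocol article*

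**What the plan says.** The Statistical methods section of the protocol article gives one sentence to the cost endpoint: "The total cost per patient will be analysed using Wilcoxon’s signed ranks test". It names no other test for total cost. The same section limits the weight of this analysis: "Secondary and tertiary analyses are exploratory and will be performed descriptively".

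The comparison intended is set out under Primary and secondary study endpoints: "differences in the total cost of treatment between the two groups will be compared". The data to which the test would be applied are described elsewhere:

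- Abstract, Methods/Design: a "randomised controlled trial with a parallel design".
- Randomisation/blinding: "A randomisation list is created and assigns the patients to either the control group or the study group".
- Study population: "A total of 68 men or nonpregnant women scheduled for primary unilateral TKR will be recruited".
- Study procedure, Table 1: the row "Calculation of overall costs of TKR" is marked in one column only, the 12-month visit.

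**The concern.** The signed-rank test needs either pairs of observations or a single sample with a reference value. A parallel-group trial with one cost per patient gives two independent samples. An analyst who followed the sentence literally would have to invent pairs, for example by list order, and nothing in the protocol says how.

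What is at stake is limited to the cost result. The influence of EVICEL on overall cost is the tertiary objective, and this is the only test named for total cost. The Statistical methods section also attaches the word significant to P values below 0.05, even though they are to be read descriptively. A P value that changes with the pairing could therefore be labelled either way.

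**Working it through.** **1. Does any feature of the design supply pairs?**

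| Possible source of pairs | What the protocol article describes | Pairs? |
|---|---|---|
| Crossover, both treatments in one patient | Parallel groups (Abstract; Study design) | No |
| Two knees in one patient | Unilateral surgery (Study population) | No |
| Before and after in one patient | One overall cost, at 12 months (Table 1) | No |
| Matched patients | Individual assignment from a list, no matching mentioned (Randomisation/blinding) | No |
| One sample against a reference cost | No reference cost given; the comparison is between the groups (Primary and secondary study endpoints) | No |

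None of the routes to a signed-rank test is open.

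**2. What the two tests compute.** Let x₁…x₃₄ be the EVICEL costs and y₁…y₃₄ the control costs.

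- Signed rank: form dᵢ = xᵢ − yᵢ, rank the |dᵢ|, and sum the ranks of the positive dᵢ. The result depends on which y stands beside which x. With 34 per arm there are 34! ≈ 2.95 × 10³⁸ ways to pair, and the protocol singles out none.
- Rank sum: U = number of (i, j) with xᵢ > yⱼ, counting ties as one half, over all 34 × 34 = 1,156 cross-arm comparisons. No order is needed, and the arms may differ in size.

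**3. Unequal arms.** With 34 costs in one arm and 33 in the other, the paired differences cannot be formed, and the software call stops with an error. Unequal numbers are possible. The Sample size calculation section expects no drop-outs only for the 7-day haemoglobin endpoint, whereas cost is completed at 12 months. The Study design section does aim for 34 completers per group, which would equalise a completers-only analysis. The numbers randomised need not be equal.

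**4. Equal arms with arbitrary pairing (illustration).** The protocol gives no cost figures, so the distribution is assumed: log-normal, log SD 0.4, 34 per arm, log means 9 and 9.2. One data set was held fixed and re-paired at random 5,000 times.

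- Rank-sum P value: 0.097, a single value.
- Signed-rank P value: median 0.125, central 95% range 0.037 to 0.263, extremes 0.005 and 0.61.
- Share of pairings with P below 0.05: 5.9%.

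**5. Error rates** (10,000 simulated trials, same log SD, one blind pairing per trial):

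| Log shift (cost ratio) | Signed rank, P < 0.05 | Rank sum, P < 0.05 |
|---|---|---|
| 0 (1.00) | 0.050 | 0.048 |
| 0.2 (e^0.2 = 1.22) | 0.480 | 0.500 |
| 0.3 (e^0.3 = 1.35) | 0.825 | 0.845 |

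The first row is as theory predicts. If the two cost distributions are identical and the pairing ignores the costs, each dᵢ is symmetric about zero, which is what the signed-rank test requires. The power loss is about 0.02 (0.500 − 0.480; 0.845 − 0.825).

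**6. Does any stated figure move?** The only sample-size figure is for the haemoglobin decrease: difference 37 − 25 = 12 g/l, SD 15 g/l, two-sided 0.05, power 90%. The normal approximation gives n = 2 × (1.960 + 1.282)² × 15² / 12² = 32.8, so 33 per group. The exact t calculation gives power 0.893 at 33 and 0.902 at 34, which reproduces the stated 34. Cost does not enter it.

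**The case against.** The strongest reply is that this is a slip of name. The intended comparison is stated as between groups, and the neighbouring analyses (t-tests, log rank tests, odds ratios) are two-group methods. A statistician would probably run the rank-sum test without hesitation. That is likely, but it does not make the sentence right: the test it names is a real and different one, and no other part of the article corrects it. A separate analysis plan may exist, but this is a rule the article states wrongly, not a detail it leaves out.

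A second reply is that the analysis is exploratory and descriptive. That stands, and it settles the size of the point. The primary ANCOVA, the superiority rule and the sample size do not depend on it.

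A reader might also infer more than the documents support:

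- *That the test would produce false positives, or a P value reflecting row order instead of the data.* It reflects both, and with pairing done blind to the costs the type I error is near 0.05.
- *That the extremes of 0.005 and 0.61 measure the impact.* They are the minimum and maximum over many pairings of one simulated data set and widen as pairings are added. The central range is the fairer description, and it too rests on assumed costs.
- *That the tertiary objective has no other analysis.* Length of hospital stay, which the endpoints section treats as part of the cost evaluation, has its own t-test.
- *That a mean cost difference is required.* The Abstract speaks of reducing costs, but the Trial objectives section asks only what influence EVICEL has on overall cost. Choosing the mean as the main summary is a separate preference.

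**Conclusion.** The named test does not fit the design. A signed-rank test is undefined for two independent groups with one cost each: it cannot be run with unequal arms, and with equal arms its P value varies with a pairing that nothing in the protocol determines. This follows from the design as described and does not depend on the simulation.

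The size is small. The fault affects the only test named for total cost, an exploratory endpoint. Under the assumed log-normal costs and blind pairing, type I error is unchanged for practical purposes and power falls by about 0.02; the remaining harm is that the reported P value is arbitrary. Reading this as a threat to the trial's main conclusion would go beyond the documents, because no primary analysis or sample-size figure is touched. It is a minor but real correction.

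**What to change.** In Statistical methods, replace the signed-rank test with the two-sample version, for example: *Total cost per patient will be compared between the groups with the Wilcoxon rank-sum (Mann-Whitney) test for independent samples.*

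Optionally, add the difference in mean total cost with a bootstrap 95% confidence interval as a descriptive result, since a rank test does not express a saving in money. The details can sit in the analysis plan.

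The correction costs one sentence. It changes no data collection, sample size or primary analysis, and the Trial status section reports that recruitment has not begun. The optional summary adds one exploratory analysis.

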### Trial objectives

This randomised controlled study has three main objectives. The primary objective is to test the null hypothesis that the effect of EVICEL™ on controlling haemostasis and reducing postoperative blood loss in patients undergoing TKR is no different than with the use of standard orthopaedic surgery. The secondary objective is to show that EVICEL™ reduces the need for transfusion and increases ROM when measured 7 days after surgery and in the long term, improves wound healing and reduces the need for analgesics. In addition, two clinical outcome scores will be assessed.

The tertiary objective is to determine the influence of EVICEL™ use on the overall cost of TKR treatment.

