## Trial status

This RCT was designed as an investigator-initiated study for which Hannover Medical School was assumed to be acting as sponsor. The study was funded by Ethicon Inc., the parent company of Omrix Biopharmaceuticals, which produces the IMP. A contract was signed and initial financial support was provided according to the contract terms, which included approval by the Independent Ethics Committee. Approval by the national competent authority was not obtained following feedback from the European Medicines Agency. When the issues were resolved, the study was prepared for resubmission to the national competent authority. However, in the meantime, ETHICON changed their business strategy and further funding was withdrawn. Therefore, the study has not yet started patient recruitment.

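### Total cost per patient is to be analysed only by a rank test, which does not estimate the difference in mean cost that the cost objective asks about

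*Protocol article*

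**What the plan says.** The abstract states the cost aim as a direction: "The tertiary objective is to show that EVICEL™ reduces the costs of total knee replacement treatment". The Trial objectives section states it neutrally: "The tertiary objective is to determine the influence of EVICEL™ use on the overall cost of TKR treatment". The section on primary and secondary endpoints says that "differences in the total cost of treatment between the two groups will be compared, including the need for physiotherapy".

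The Statistical methods section then names one analysis for this endpoint: "The total cost per patient will be analysed using Wilcoxon"'s signed ranks test. It attaches no effect measure or interval. In the same paragraph, by contrast, "the need for at least one transfusion will be analysed by odds ratios (OR) together with 95 % CIs", and range of motion and length of stay get t-tests, which compare means. The section adds: "Secondary and tertiary analyses are exploratory and will be performed descriptively".

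**The concern.** Both versions of the objective concern overall cost. For a hospital or payer that is the number of patients multiplied by the arithmetic mean cost, so the relevant quantity is the difference in mean cost per patient, in money.

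A rank comparison answers another question: does a randomly chosen EVICEL patient tend to cost more than a randomly chosen control? It yields no amount of money. It gives full weight to a small shift in every treated patient and little weight to the size of a few large savings. Every study patient receives the sealant, so a shift of the first kind is present by design. If savings came mainly from a few expensive patients, the ranks and the means could disagree, and a reader could take the P value as an answer about cost in the wrong direction.

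The named test is also the paired form, although the two arms are independent. Changing to the rank-sum test cures the pairing fault but leaves the present one in place.

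**Working it through.** **The plan's own figure.** The document gives no cost figure: no mean, SD, difference or power. Its only sample-size figure is for haemoglobin. With a difference of 37 − 25 = 12 g/l, SD 15 g/l, two-sided 5% and 90% power, the normal approximation is n = 2 × (1.96 + 1.2816)² × 15² / 12² = 32.8, so 33 per group. The exact noncentral t gives power 0.893 at 33 and 0.902 at 34, so the stated 34 reproduces. Cost plays no part in it.

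**Illustrative inputs (all assumed, arbitrary currency).** 34 per arm (from the protocol). Routine cost is lognormal with mean 9,000 and SD 1,000, 1,500 or 2,500. An event costing 10,000 occurs in 15% of controls and 5% of EVICEL patients. The sealant adds 800 (or 500) to each treated patient.

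**Step 1, true mean difference (EVICEL minus control).**
- Add-on 800: 800 − (0.15 − 0.05) × 10,000 = −200.
- Add-on 500: 500 − 1,000 = −500.

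EVICEL is cheaper on average in both.

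**Step 2, what ranks see (add-on 800).** Approximate routine cost by a normal distribution. When neither patient or both have the event (probability 0.85 × 0.95 + 0.15 × 0.05 = 0.815), the treated patient is dearer with probability Φ(800 / (SD × √2)). When only the treated patient has it (0.85 × 0.05 = 0.0425), the treated patient is almost always dearer. When only the control has it, almost never.
- SD 1,000: 0.815 × Φ(0.566) + 0.0425 = 0.815 × 0.714 + 0.0425 = 0.62
- SD 1,500: 0.815 × Φ(0.377) + 0.0425 = 0.815 × 0.647 + 0.0425 = 0.57
- SD 2,500: 0.815 × Φ(0.226) + 0.0425 = 0.815 × 0.590 + 0.0425 = 0.52

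All exceed 0.5, so the ranks lean towards EVICEL being dearer while its mean is lower.

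**Step 3, simulated two-sided rank-sum test at 0.05.**

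| Add-on (true difference) | SD 1,000 | SD 1,500 | SD 2,500 |
|---|---|---|---|
| 800 (−200): significantly dearer | 43% | 18% | 6% |
| 800 (−200): significantly cheaper | at most 1% | at most 1% | at most 1% |
| 500 (−500): significantly dearer | 15% | 6% | 2.5% |
| 500 (−500): significantly cheaper | 0.2% | 0.9% | 2.5% |
| 800: significantly dearer and observed EVICEL mean lower | 12% | 1% | 0% |

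**Step 4, other concentrated-savings inputs.** Twelve scenarios were run with base cost 10,000, add-on 500 to 800, an event of 15,000 in 10–15% of controls against 3–5% of treated patients, and a coefficient of variation of 5–20%. The true difference was −250 to −1,000, and the probability that a treated patient is dearer was 0.51 to 0.75. A significant dearer result with a lower observed EVICEL mean occurred in 0.1% to 71% of runs.

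**Step 5, the opposite pattern.** Suppose each treated patient saves 1,500, the add-on is 500 and the event rate is 5% in both arms (true difference 500 − 1,500 = −1,000). The rank-sum test then finds EVICEL cheaper in 68% and 33% of trials (SD 1,500 and 2,500), against 37% and 25% for a Welch t-test on means. It practically never finds it dearer.

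**Step 6, precision of the mean difference (Step 1 inputs, either add-on).** The event variances are 0.15 × 0.85 × 10,000² = 12.75 million and 0.05 × 0.95 × 10,000² = 4.75 million. The 95% half-width is 1.96 × √((2 × SD² + 17.5 million) / 34).
- SD 1,000: 1.96 × √(19.5 million / 34) = 1,484
- SD 1,500: 1.96 × √(22 million / 34) = 1,577
- SD 2,500: 1.96 × √(30 million / 34) = 1,841

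Against a true difference of 200, a test on means detects the saving in about 3% of trials.

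**The case against.** **No estimate is excluded.** The article condenses a fuller protocol, calls these analyses descriptive and says that cost differences will be compared. A reader might infer that mean cost will never be reported; the text does not say that. What stands is narrower: this document plans no cost estimate, and the one analysis it fixes has the wrong target. Elsewhere in the same section the word descriptive is attached to chi-squared tests and P values, so it does not promise a mean difference.

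**Reversal depends on assumed costs.** This stands. The Background section expects better healing, less analgesic use and shorter stays, which could spread over many patients. In that case the rank test points the right way and can be more powerful than a test on means (Step 5). The 43% also compares the test with the true mean, which no single trial observes; a visible clash with the trial's own means is less common in that scenario (12%, 1% and 0%).

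**The proposed estimate would often not settle the sign.** This also stands (Step 6). That limit comes from 34 per arm. A wide interval in money is still more informative than a P value on ranks.

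**A further inference to resist.** A reader might suspect that the product's price is left out of the total, given the funder's link to the manufacturer. The documents do not support this. They speak of total and overall treatment cost, they record the volume of sealant used, and nowhere do they say that it is supplied free or excluded.

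**Conclusion.** The point holds in limited form. The named rank test does not estimate the mean cost difference that the objective concerns, and replacing the paired form with the two-sample form does not change this. The ranks can oppose the means when a product cost falls on every treated patient and savings fall on a few. How often depends wholly on cost inputs that the documents do not give: on the assumptions tried, a clash with the trial's own observed means ranged from about 0% to 71% of runs. The figures show that reversal is possible; they do not predict it, and with diffuse savings it need not occur.

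The consequence is confined to the conclusion on cost, a tertiary and exploratory endpoint. The primary haemoglobin analysis and the 34 per group are unaffected. This is a cheap improvement and not a threat to the trial.

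**What to change.** In Statistical methods, replace the cost sentence with one to this effect: the cost result is the difference in arithmetic mean total cost per patient, EVICEL minus control, with a bootstrap 95% confidence interval resampled within arm; a two-sample Wilcoxon rank-sum test may be reported as a supplement.

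This takes one sentence and a few lines of code, needs no new data and does not change the sample size. The price is a wide interval that will often include zero, and the report should say so plainly.
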